## Abstract

**Background:**

Lymphedema is a common complication following breast cancer treatment. The aim of this study is to evaluate the effectiveness of a self-adjusting compression garment (ReadyWrap®) in reducing (phase 1) and maintaining (phase 2) upper limb volume in women presenting breast cancer-related lymphedema.

**Methods:**

This study will comprise a randomized, controlled, single-blind clinical trial concerning women with breast cancer-related lymphedema undergoing treatment at a public cancer treatment reference hospital in the city of Rio de Janeiro, Brazil. The intervention will be carried out by adapting self-dressing versus the standard treatment of compressive bandaging (phase 1) and compressive mesh (phase 2). Both groups will be assessed at the beginning and end of intensive treatment and followed up for up to 12 months to evaluate immediate and late outcomes. Assessments will be carried out by physical upper limb examination (inspection, palpation, volume, dynamometry, and thermography) and questionnaires application to assess patient’s quality of life pertaining to the health, functionality, and symptoms of the affected upper limb, as well adverse effects and adherence to treatment. Data will be analyzed descriptively and analytically through univariate and multiple linear regressions. *P* values < 0.05 will be considered statistically significant.

**Discussion:**

This study will evaluate the effectiveness of a self-adjustable garment (ReadyWrap®) in the treatment of lymphedema secondary to breast cancer in Brazilian women compared to the gold standard treatment for limb volume reduction (phase 1) and maintenance (phase 2) phases comprising, respectively, a compressive bandaging and a compressive mesh. The outcome results will provide data based on both quantitative responses and self-reported participant outcomes. The study will also assess the cost-effectiveness of the ReadyWrap® treatment versus standard care. Finally, we expect to reaffirm one more product/therapy as a treatment for this extremely complex and impactful condition following the data analysis.

**Trial registration:**

NCT04934098 [Clinical trials phase 1]. Registered on June 22, 2021. NCT04881604 [Clinical trials phase 2]. Registered on May 11, 2021.

## Administrative information

Note: the numbers in curly brackets in this protocol refer to SPIRIT checklist item numbers. The order of the items has been modified to group similar items (see http://www.equator-network.org/reporting-guidelines/spirit-2013-statement-defining-standard-protocol-items-for-clinical-trials/).

## Introduction

### Background and rationale {6a}

One of the main late breast cancer treatment-associated complications is lymphedema, a chronic progressive condition that can develop months or years after treatment. This condition generally affects 1 in 5 women, and its risk increases in patients undergoing radiotherapy, affected limb chemotherapy infusion, obese women, patients presenting seroma development after surgery, a greater number of removed lymph nodes, or presenting an advanced disease stage at diagnosis [1–4]. According to a study carried out with a cohort of Brazilian women, the cumulative incidence of lymphedema ranges from 13.5% in 2 years to 41.1% in 10 years [2].

Breast cancer-associated lymphedema results from lymphatic system impairment due to lymphatic fluid drainage obstruction and/or interruption, which leads to the accumulation of protein-rich fluids in interstitial spaces, resulting in local edema in the affected area. This phenomenon can affect the upper limb ipsilateral to the surgery, as well as the chest wall and scapular region [3, 5]. When untreated, edema causes progressive structural skin distortion, such as thickening and loss of elasticity, as well as sensory alterations, and pain, also increasing the risk of infections [5]. Because of this, women with this condition present a variety of physical and psychosocial problems, leading to daily activity limitations and negatively affecting their functionality and quality of life [1, 3, 6, 7].

In this context, lymphedema treatment should be initiated at the first signs, aiming towards a better clinical condition resolution and lower quality of life impacts. The gold standard treatment for lymphedema recommended by the International Society of Lymphology [8] is complex decongestive therapy (CDT), consisting in a combination of manual lymphatic drainage, compression therapy, therapeutic exercises, and skin care [4, 9].

Compression therapy is one of the main therapeutic physiotherapy resources to reduce lymphedema-affected limb volume and improve fibrosclerotic changes. This method consists of two distinct phases, the first aiming to maximize limb volume, traditionally performed with compressive bandages, and the second aiming to maintain limb volume, replacing the bandage by a compressive mesh [5, 9].

Studies have established the use of self-adjusting garments to replace or complement the use of bandages and/or compressive meshes [10, 11]. These garments are defined as a prefabricated system consisting of inelastic material containing self-adjusting compressible components according to the size and shape of the patient’s upper limb, comprising one of their main advantages, as these garments can be adapted by the patients themselves, allowing for adjustments with decreasing limb volumes [11]. Thus, costs associated to individual consultations can be minimized while still maintaining lymphedema control effectiveness. These garments can also be potentially useful for patients who live far from treatment centers or who present functional or social difficulties in commuting.

Few studies, however, have evaluated the effectiveness of compression therapy employing self-adjusting garments compared to compressive bandages in the volume reduction phase (phase 1) and meshes in the volume maintenance phase (phase 2) of upper limbs presenting lymphedema secondary to breast cancer.

### Objectives {7}

The primary aim of this study is to evaluate the effectiveness of a self-adjusting compression garment (ReadyWrap®) in reducing and maintaining upper limb volume in women presenting breast cancer-related lymphedema compared to standard compression therapy. Secondary objectives consist in comparing upper limb volume and tissue changes, muscle strength, functionality, and symptoms, as well as health-related quality of life, while also assessing the incidence of adverse events, treatment adherence, and material and professional costs according to the intervention group.

### Trial design {8}

The trial design is as follows: single-blind, superiority, randomized controlled clinical trial, with a 1:1 allocation ratio for each group. Phase 1 participants cannot be part of phase 2 study and vice versa.

## Methods: participants, interventions, and outcomes

### Study setting {9}

This is a clinical trial developed in a public cancer treatment reference hospital in the city of Rio de Janeiro, Brazil, which will compare the standard lymphedema treatment with a self-adjusting compression garment according to treatment phase (upper limb volume reduction or maintenance).

### Eligibility criteria {10}

Women aged 18 years and older diagnosed with upper limb lymphedema following surgical breast cancer treatment over 6 months previously and evaluated by the hospital’s physiotherapy service will be eligible for the study. The inclusion criteria were defined according to breast cancer-associated lymphedema treatment stages (Table 1):

**Table 1 Tab1:** Inclusion criteria

Treatment phase	Inclusion criteria
**Phase 1: Volume reduction**	Women with volume changes ≥ 10% or perimetry differences ≥ 3 cm in at least one point compared to the contralateral limb, with an indication of compressive bandaging according to the institutional routine [12]
**Phase 2: Volume maintenance**	Women with stabilized lymphedema with an indication of compressive mesh according to the institutional routine [12]

The following will be excluded from both treatment phases: women presenting the following: lymphedema prior to surgery; lymphedema or bilateral lymphadenectomy; phlogistic signs in the swollen limb; submitted to compressive bandaging in the last 3 months; previous history of allergic reaction to the material employed used in compression therapy; locally, regionally, or remotely active disease; undergoing chemotherapy or radiotherapy; presenting functional upper limb changes prior to the breast cancer diagnosis; presenting heart disease and uncompensated systemic arterial hypertension; psychiatric, mental, and neurological disorders or any cognitive impairment that make answering questionnaires impossible.

### Who will take informed consent? {26a}

Eligible candidates will be invited by sector physiotherapists to participate in the study. If they agree, they will be forwarded to a space reserved for signing the free and informed consent form (FICF), an interview, and initial evaluation with the study researchers.

### Additional consent provisions for collection and use of participant data and biological specimens {26b}

Item not applicable in this research, as biological samples are not used to evaluate the study outcomes.

## Interventions

### Explanation for the choice of comparators {6b}

The control group participants will receive the standard institutional therapy, consisting of the gold standard in lymphedema secondary to breast cancer treatment. Thus, the standard intervention group comprising phase 1 will receive the compressive bandaging treatment, while the standard intervention group of phase 2 will receive the compressive mesh treatment.

### Intervention description {11a}

The evaluations, interventions, and data collection steps will be carried out by three professional physiotherapists with at least 2 years of experience in compression therapy, all trained and qualified for this purpose. All participants will be guided on the research procedures and will receive a booklet with guidance on performing daily home upper limb exercises, skin care, and daily living activities according to the applied institutional routine [12], which does not include manual lymphatic drainage. Compression therapy will be indicated according to the treatment phase (1 or 2) and intervention group (experimental or control). Participants will be randomly allocated to the following treatment groups (Fig. 1).

**Fig. 1 Fig1:**
[figure not shown]
Study schema

### Phase 1 (volume reduction)

#### Group A: Experimental intervention with the ReadyWrap® self-dressing

Participants in this group will receive the ReadyWrap® self-garment (a short-stretch compression wrap, user-adjustable through Velcro straps, which can be made up of up to 2 pieces—arm and hand), according to an ideal size indication derived from affected upper limb perimeter measurements. The garment will be used continuously, maintained for 30 consecutive days, and removed only when bathing. The evaluations will be carried out in a face-to-face consultation on the 1st, 7th, and 30th day after the adaptation period.

A booklet and video were produced exclusively with guidelines on the use of the self-garment and will be made available to participants.

#### Group B: Standard compressive bandaging intervention

This group of participants will receive the standard compressive bandaging treatment for upper limb volume reduction. The compressive bandaging consists of adapting low-elastic bandages placed in layers (multilayer) throughout the affected limb. The upper limb will first be cleaned and hydrated and a tubular mesh will then be worn for protection and for minimizing the risk of allergic reactions. The foams will then be adapted to give the limb a cone shape and soften bone points, contributing to regular pressure distribution. Finally, the bandages will be adapted from the distal to the proximal part. The compressive bandaging will be used continuously for 30 days, changed twice a week in face-to-face consultations. The evaluations will take place on the 1st, 7th, and 30th day after adaptation.

### Phase 2 (volume maintenance)

#### Group C: Experimental intervention with the ReadyWrap® self-dressing garment

The participants in this group will be submitted to a similar treatment as group A, although with the aim of maintaining upper limb volume. The patients will be instructed to remove their garment during nightly sleep, in addition to bath time. After 7 days of self-garment adaptation, the research team will contact the patients by phone to monitor possible adverse events and assess the need for face-to-face consultations. Outpatient follow-up and evaluations in face-to-face consultations will take place on the 1st and 30th day after adaptation.

#### Group D: Standard compressive mesh intervention

This group will receive the standard upper limb volume maintenance treatment employing a compressive mesh that provides 30 to 40 mmHg of pressure and has an elastic Velcro strap for fixation that will be adapted according to ideal size indications following affected upper limb perimetry measurements. The compressive mesh must be continuously used, removing the mesh only for bathing and night sleeping. After 7 days of adaptation, the research team will contact the patients by phone to monitor possible adverse events and assess the need for face-to-face consultations. Outpatient follow-up and evaluations in face-to-face consultations will take place on the 1st and 30th day after adaptation.

Participants in each intervention group will be followed and reassessed 6 and 12 months after study enrollment to verify long-term outcome measures. At the end of this period, the standard compressive mesh will be adapted and provided free of charge according to the applied institutional routine.

### Criteria for discontinuing or modifying allocated interventions {11b}

Treatment suspension before the proposed period will be implemented when side effects occur, such as allergic reactions or poor adaptation to the employed material, as well as limb volume increases greater than 10% of the initial volume, affected upper limb infection and decompensated systemic blood pressure. In the case of any other unforeseen changes, the patient will be evaluated by the health team and any necessary procedures will be adopted.

### Strategies to improve adherence to interventions {11c}

With the aim of improving treatment adherence, the volunteers will receive a therapeutic diary for use in the first 30 days, in which they must notify exercise performance, garment use, and any arm symptoms during treatment daily. In addition, a face-to-face consultation for the phase 1 groups (A and B) and a teleconsultation for the phase 2 groups (C and D) will be performed within 7 days of study inclusion.

### Relevant concomitant care permitted or prohibited during the trial {11d}

It is important to note that any other lymphedema treatment intervention employed by the study participants will not be restricted. Patients should carry out their normal routines and the only interference of this study will be the type of provided compression therapy. Thus, all patients will be instructed to only use the provided compression therapy.

### Provisions for post-trial care {30}

If an increase of over 10% of the initial volume of the upper limb presenting lymphedema is observed during the 30-day reassessment after participant inclusion, compromising patient functionality and/or quality of life, the participant will be directed to the standard treatment offered by the institution’s physiotherapy service. At the end of the study, regardless of the allocation group and results, participants will be directed to lymphedema treatment according to the institutional routine.

## Outcomes {12}

### Primary outcome

#### Lymphedema arm volume

This will be evaluated by determining upper limb perimetry, with reference to the cubital fold, from which points will be measured at 7 cm, 14 cm, and 21 cm below and 7 cm and 14 cm above. The measurements referring to each point will be applied in the trunk cone formula *V* = *h* * (*C*^2^ + *Cc* + *c*^2^)/(π* 12), where *V* is the limb segment volume, *C* and *c* are the circumferences at each end, and *h* is the distance between circles (*C*). This calculation will represent the estimated limb volume [13]. The limb volume percentage reduction will be calculated as (*VI*-*VF*/*VI*)*100, where *VI* comprises the initial volume and *VF* the final volume. The treatment response will be considered effective in phase 1 when an affected upper limb volume reduction of over 10% of the initial volume takes place, while phase 2 therapy success will be linked to volume maintenance or a greater variation of up to 10% of the initial volume of the upper limb presenting lymphedema.

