### Sample size {14}

Considering the benefits of complex physical therapy when there is a percentage reduction in excess limb volume of 22% to 73% [21], and, for the use of compressive therapy, an estimated response of 33.5% reduction in excess limb volume [22], we stipulated a 35% variation in treatment response between the groups, with an estimated treatment response of 45% in the control group (standard care) and 80% in the intervention group. The sample size was calculated considering a confidence level of 95% with a study power of 80% and a 1:1:1:1 ratio between the intervention groups. Thus, a total population of 120 patients (30 in each group) will be required. To cover possible losses to follow-up and treatment interruption, a total of 20% will be added to the number of participants Therefore, the total sample to be included in this study will be of 144 women (36 in each group).

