## Statistical methods

### Statistical methods for primary and secondary outcomes {20a}

A descriptive analysis of the sociodemographic and clinical characteristics of the study population will be carried out through the distribution of absolute and relative frequencies for categorical variables and central tendency and dispersion measures for continuous variables. The thermographic analysis will be obtained by the average difference in temperatures of one limb in relation to the other and a cut-off point will be established. Data normality will be calculated using the Kolmogorov–Smirnov test. Group comparisons will be done by using Student’s *t* test or Wilcoxon test for continuous variables and chi-square test for categorical variables. The effect size of the mean outcomes will be calculated using Glass’s delta (considering 0.2 as small, 0.5 as medium, and 0.8 as large effects) [23]. Associations between the variables of interest and the outcome will be performed using univariate linear regression. Variables presenting *p* ≤ 0.20 will be included in the multiple linear regression model employing the stepwise forward method, and those with *p* < 0.05 or with clinical relevance will be maintained in the adjusted model. A significance level of 5% will be accepted, at a confidence interval of 95%. Statistical tests will be performed using the SPSS version 23.0 software.

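### Arm volume is the named primary outcome, but effectiveness is a 10% cut, the sample size is for proportions, and no comparison is named as deciding superiority

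*Protocol article*

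**What the plan says.** Under Outcomes {12}, the primary outcome is arm volume estimated from perimetry. A change score follows ("The limb volume percentage reduction will be calculated as" the difference between initial and final volume, relative to initial volume). The same paragraph then sets a yes/no rule for each phase. The phase 1 rule begins "The treatment response will be considered effective in phase 1 when an affected upper limb volume reduction of over 10% of the initial volume takes". For phase 2, the text says "phase 2 therapy success will be linked to volume maintenance or a greater variation of up to 10% of the initial volume". The reference in that paragraph is attached to the volume estimate, and no rationale is given for 10%.

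Sample size {14} works only with response proportions. It fixes the difference ("we stipulated a 35% variation in treatment response between the groups"), then the two rates behind it ("an estimated treatment response of 45% in the control group (standard care) and 80% in the intervention group"), and then the error settings ("considering a confidence level of 95% with a study power of 80% and a 1:1:1:1 ratio between the intervention groups"). This gives 30 per group, raised to 36 for losses. No mean difference or SD appears. The section does not mention the 10% cut, and the published figures it draws on are percentage reductions in excess limb volume, whereas the cut is on initial limb volume.

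Statistical methods {20a} states: "Group comparisons will be done by using Student’s *t* test or Wilcoxon test for continuous variables and chi-square test for categorical variables". It adds Glass's delta for mean outcomes and univariate, then multiple, linear regression. The abstract's Methods names only the linear regressions. Trial design {8} declares superiority.

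**The concern.** Three parts of the protocol sit on two scales. The outcome is continuous, effectiveness and sample size are binary, and most of the listed analysis is continuous again. A mean difference can be significant when the responder difference is not, or the reverse, and nothing says which result would establish superiority. Participants and research physiotherapists know the allocation, and an analysis of the 30-day data is planned, so the choice should be fixed before groups are compared.

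If the cut does carry the decision, it discards information: a 10.1% and a 40% reduction count the same, and a 9.9% reduction counts the same as an increase. With about 30 evaluable women per group, that could matter.

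**Working it through.** **Inputs.** From Sample size {14}: 45% vs 80%, 80% power, 95% confidence, 30 evaluable per group. Assumptions, because the protocol does not give them: two-sided testing, the SD and shape of percentage change, and that 45%/80% are the rates of passing the 10% cut.

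**1. The stated sample size.** Formula: n = [1.960·√(2·p̄·q̄) + 0.842·√(p1q1 + p2q2)]² / (p2 − p1)², with p̄ = 0.625.
- √(2 × 0.625 × 0.375) = 0.685
- √(0.45 × 0.55 + 0.80 × 0.20) = 0.638
- n = (1.342 + 0.537)² / 0.35² = 3.531 / 0.1225 = 28.8, so 29 per group

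The stated 30 is reproduced, as a two-proportion calculation without continuity correction.

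**2. Power of the binary comparison.** At 30 per group, uncorrected chi-square has 81.6% power (normal formula and exact enumeration agree). With Yates' correction or Fisher's test it is 73.8%. At 36 per group, exact uncorrected power is 88.8%.

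**3. Power of the continuous comparison, phase 1, one threshold, normal, common SD.**
- Implied shift: z(0.80) − z(0.45) = 0.842 + 0.126 = 0.967 SD
- Noncentrality at 30 per group: 0.967 × √(30/2) = 3.75 on 58 degrees of freedom
- t-test power: 95.8%, which is 14.2 points above 81.6%
- At 36 per group: 98.2% against 88.8%
- Smallest difference detectable with 80% power at 30 per group: about 0.74 SD

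**4. Sensitivity to SD and shape.** The 45%/80% rates and 30 per group are kept. With intervention SD = r × control SD, the shift is 0.126 + 0.842r control SDs. Chi-square power stays at 81.6%.

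| Assumption | t-test power | Difference (points) |
|---|---|---|
| r = 0.5 | 75% | about -7 |
| r = 0.75 | 90% | about +8 |
| r = 1 | 96% | about +14 |
| r = 1.5 | 98.5% | about +17 |
| t tails, 5 df | 87% | about +5 |
| t tails, 3 df | 75% | about -7 |

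**5. Phase 2.** Suppose success means staying within ±10%, with 45% vs 80% doing so. If the arms differ only in spread, a t test on mean change has about 5% power. If they differ only by a mean shift with common SD, it has more than 99.9%. The phase 1 conversion therefore does not carry over.

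**6. Leaving both tests open.** Simulating no group difference (normal outcome, 30 per group) and claiming success if either the t test or uncorrected chi-square gives p < 0.05, the type I error is about 7.5% to 8.3% instead of 5%. It was 7.8% in a run of 200,000 replicates with a common response rate of 45%, and 8.3% at 80%.

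**The case against.** The strongest reply is that no power need be lost. A reader might infer that the chi-square on responders is the primary test and that the cut costs 14 points of power in each phase. The protocol does not support that reading. It names arm volume as primary, and Glass's delta and linear regression fit a continuous outcome. If the continuous analysis decides, the cut costs nothing. That 45%/80% are rates at the 10% cut is also an inference. The 14 points need a normal outcome with common SD, and phase 2 may be a two-sided window for which staying within tolerance is itself the question. All of this stands.

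It can also be said that a responder endpoint is legitimate and easy to read, that 10% recurs as the protocol's own threshold for worsening, and that the stated power is reached. This stands too, though reusing a threshold does not justify it as a criterion of benefit.

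Finally, the choice of primary test might be left to an analysis plan that is not shown. That would excuse silence. It does not remove the mismatch within this document: if the continuous analysis decides, Sample size {14} powers a different comparison; if the responder analysis decides, the regression and effect-size methods do not address it.

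**Conclusion.** The point holds as a mismatch between outcome, sizing and analysis, with no comparison named as decisive. Using whichever test succeeds would put the type I error at roughly 7.5% to 8.3%. The efficiency cost is conditional and applies to phase 1 only. If the cut decides and 45%/80% refers to it, power is 81.6% against 95.8% under a normal outcome with common SD, with the difference ranging from about -7 to +17 points over the other shapes tried. No stated figure fails: the 30 per group reproduces and gives at least 80% power with the uncorrected test. This is a defect of consistency and efficiency, worth correcting because the correction is cheap.

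**What to change.** - **Outcomes {12} and Statistical methods {20a}, phase 1:** name as the primary comparison the between-group difference in affected-limb volume (or its percentage change), from a linear model with randomised group and baseline volume, with its 95% CI. Report the 10% response proportion as a supporting outcome with a risk difference and CI.
- **Sample size {14}:** keep 36 per group. Add that 30 evaluable per group gives 80% power for about 0.74 SD. Label any conversion from 45%/80% to an SD shift as an assumption.
- **Phase 2:** first reconcile whether success is a one-sided limit or a two-sided window, then name one primary comparison that fits. Do not carry over the phase 1 power figures.
- **Timing:** make the change before any group comparison, including the 30-day analysis under Interim analyses {21b}.

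The cost is wording: no extra participants, visits or measurements. The small downside is that the headline becomes a mean difference, so the responder rate must be shown beside it for clinical reading.
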